## Abstract

Evidence-based practice (EBP) combined with quality of care improves patient outcomes. However, there are still difficulties for its implementation in daily clinical practice. This project aims to evaluate the impact of the incorporation of the Advanced Practice Nurse (APN) role on the implementation of EBP at three levels: context, nurses’ perceptions, and clinical outcomes. Mixed-methods study in two phases is proposed. Phase 1: a quasi-experimental design where five APNs are included in five hospitalization wards that are compared with another five similar wards without APNs. Variables from Practice-Environment-Scale-Nursing-Work-Index, Health-Science-Evidence-Based-Practice-Questionnaire, and Advanced-Practice-Nursing-Competency-Assessment-Instrument are used. Clinical outcomes are followed-up with monthly. A descriptive and exploratory analysis is performed. Phase 2: an exploratory qualitative design through focus groups at the intervention wards after one year of APNs implementation. Explicative data are gathered to explain the progression of change and how actors perceive and attribute triggers, barriers, and facilitators for change. An inductive thematic analysis is performed. The inclusion of APN in hospitalization context is insufficiently studied. It is hoped that these figures provide solutions to the multiple barriers in the development of EBP in these sceneries and contribute to resolve the gap between research results and healthcare practice.

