### 2.2. Settings

Ten medical and surgical hospital wards were selected in three public hospitals managed by the Balearic Islands health service—a university hospital and two regional hospitals. Intervention and control groups were created, each consisting of three medical and two surgical wards.

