### 2.5. Sample and Participants

The quantitative phase started with registered nurses working in the hospital wards included in the study in addition to the APHNs and their supervisors working in the intervention wards. The qualitative phase is carried out only with the nurses of the intervention group, the APHN, and the supervisors.

The sample size needed for the quantitative phase was calculated according to the difference of expected scores of the PES-NWI questionnaire on organizational traits (Supplementary Appendix 1). The calculation was performed for independent means, assuming an alpha risk of 0.05 and a beta risk of less than 0.2 in bilateral testing. Therefore, to detect a difference equal to or greater than four points, 70 subjects are needed in each of the study groups, assuming a standard deviation of eight and a loss rate of 10%. In the Health Service of the Balearic Islands, there are about 15 nurses per hospital unit, thus each study group corresponds to five hospital wards.

In the qualitative phase, six focus groups are carried out: one focus group with the APHNs and five focus groups with nurses, one in each of the five units where the figure of the APHN is implanted. Sampling for the focus groups of nurses is intentional, and a minimum of six and a maximum of 12 nurses are recruited in each of the units. The five APHNs and at least three to five support nurses are included in the APHN focus group.

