### 2.8. Data Analysis

Descriptive and exploratory analyses of the quantitative data will be performed, determining, among other parameters, the main indices of central tendency, dispersion, and shape. In addition, an analysis of missing values will be conducted. The association between variables will be determined according to the scale of their mean values. A stratified analysis will be carried out using the Mantel and Haenszel test, among others (stratifying according to the possible confounding variables). Bivariate analysis will be performed to detect significant associations between the main variables and sociodemographic, occupational, and complementary variables. Multivariate analysis will also be carried out using regression models. The mean values obtained will be compared by ANOVA or the nonparametric equivalent (Kruskal–Wallis test). The main variables will be crossed with the sociodemographic variables (age, gender), the occupational variables (hospital, unit, years of experience as a registered nurse), and the complementary variables (academic qualifications). These will be analysed as possible confounders and/or modifiers of the effects produced on the study variables. Finally, an exploratory analysis of lost data will be performed. The SPSS v.22 statistical software package ( SPSS Inc., Chicago, IL, USA) will be used for all these analyses.

For the qualitative phase, a realistic thematic analysis [40] of the focus groups transcriptions will be carried out. It will be used to generate a rich description of registered nurse and APHN views on how the change process evolved and impacted the unit and patients’ outcomes and how context jeopardized and/or facilitated the process. Two researchers will analyze the data across five phases: (1) through a first process if reading, initial themes and codes will be identified and grouped and emerging patters will be checked; (2) a second process of reading and re-reading, aimed at interpreting the themes, will be conducted; (3) at this point, the two researchers will share their interpretation and will reach consensus on the list of codes and sub-codes; (4) these codes will be rechecked through a third process of reading then pieces of text that exemplify the themes will be categorized under each code. Attention will be paid to new codes that may not have been identified earlier; (5) final patterns and links will be identified among themes and codes.

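### The intervention is given to whole wards, but the sample size and the named tests treat nurses as independent, so the stated 5% error and 80% power do not hold with five wards per group

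*Protocol article*

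**What the plan says.** The comparison is between wards. In the Abstract, "five APNs are included in five hospitalization wards that are compared with another five similar wards without APNs", and section 2.2 confirms the total: "Ten medical and surgical hospital wards were selected in three public hospitals". Section 2.3 describes an intervention that works through the ward team (the APHN, a support nurse and the supervisor). Section 2.6 says that intervention wards were chosen using baseline PES-NWI and that each was paired with a control ward in the same hospital.

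The sample size in section 2.5 was "calculated according to the difference of expected scores of the PES-NWI questionnaire on organizational traits". Its model is explicit: "The calculation was performed for independent means, assuming an alpha risk of 0.05 and a beta risk of less than 0.2 in bilateral testing". The result is that "to detect a difference equal to or greater than four points, 70 subjects are needed in each of the study groups". The inputs behind it are an SD of 8 and 10% loss. The number of wards then follows from ward staffing alone: "there are about 15 nurses per hospital unit, thus each study group corresponds to five hospital wards".

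For the analysis, section 2.8 states that "The mean values obtained will be compared by ANOVA or the nonparametric equivalent" (Kruskal-Wallis). It adds a Mantel-Haenszel stratified analysis and regression models of unspecified type. Hospital and unit appear as occupational variables, to be examined as possible confounders or effect modifiers.

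**The concern.** Nurses on the same ward share a supervisor, staffing, routines and, in the intervention group, the same APHN. Section 2.4 introduces PES-NWI as the measure of organisational traits, so colleagues are largely rating the same object and their scores will tend to agree. Section 2.6 itself uses the scale as a property of wards, since wards were selected on it.

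Where scores agree within wards, two things go wrong. The nurse-level standard error is too small, so confidence intervals are too narrow and false positives exceed 5%. The information also depends mainly on the number of wards, which here came out of a formula that contains no wards. A positive PES-NWI result could then be ordinary ward-to-ward variation reported as an effect of the role, and a null result would be over-read as the outcome of an 80%-power study. Section 3 expects the findings to bear on whether the role is kept.

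The issue is the standard error and the effective sample size. It is separate from whether the ward pairs are used and from whether unit is a confounder.

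**Working it through.** **Inputs from section 2.5.** Two-sided alpha 0.05; power at least 0.80; difference 4 points; SD 8; loss 10%; about 15 nurses per ward; five wards per group.

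**Assumed.** The ICC, because the documents give none. The range 0.02 to 0.20 is used.

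**1. The plan's own figure.** n = 2 × (1.96 + 0.842)² × 8² / 4² = 62.8, so 63 per group. Allowing for loss, 63 / 0.9 = 70. The stated figure is reproduced exactly, which leaves no room for a design effect.

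**2. Design effect.** 63 analysed nurses over five wards is m = 12.6 per ward. DE = 1 + (m − 1) × ICC = 1 + 11.6 × ICC. Effective n per group = 63 / DE.

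**3. True size of a nurse-level test.** The test uses a standard error too small by a factor √DE, so its size is 2 × [1 − Φ(1.96 / √DE)]. At ICC 0.05, 1.96 / √1.58 = 1.56, which gives 0.12.

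**4. Power of a valid ward-level test.** SE = 8 × √(2 × DE / 63). Power comes from the noncentral t distribution with 2 × (5 − 1) = 8 df and noncentrality 4 / SE. At ICC 0.05, SE = 1.79 and 4 / 1.79 = 2.23, which gives power 0.50. The detectable difference is the one for which the same calculation gives 0.80.

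| ICC (assumed) | DE | Effective n per group | Size of nurse-level test | Power for 4 points, 8 df | Detectable difference, 80% power |
|---|---|---|---|---|---|
| 0 | 1.00 | 63 | 0.05 | 0.69 | 4.6 |
| 0.02 | 1.23 | 51 | 0.08 | 0.60 | 5.1 |
| 0.05 | 1.58 | 40 | 0.12 | 0.50 | 5.7 |
| 0.10 | 2.16 | 29 | 0.18 | 0.39 | 6.7 |
| 0.20 | 3.32 | 19 | 0.28 | 0.27 | 8.3 |

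**5. Check by simulation.** A nurse-level t-test on five wards of 14 nurses per group, with no true effect and 20,000 runs, rejected in 4.9%, 12.7%, 19.8% and 30.7% of runs at ICC 0, 0.05, 0.10 and 0.20. For 14 per ward the formula gives 5.0%, 12.7%, 19.6% and 30.2%.

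**6. Full response.** If all 15 nurses per ward respond (75 per group), ward-level power is 0.77 at ICC 0, then 0.66, 0.54, 0.41 and 0.28 at ICC 0.02, 0.05, 0.10 and 0.20. The size of the nurse-level test is then 0.08, 0.13, 0.21 and 0.32 at those four ICCs. The conclusion is unchanged.

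**The case against.** - **The analysis text is not closed.** Section 2.8 does not spell out that ANOVA is run on nurses for the intervention contrast, and it mentions regression models without giving their form. A condensed article may leave that to a fuller document, so a multilevel model is not ruled out. However, the tests that are named assume independent observations, none that allows for ward is named, and the sample size statement is explicit. Entering unit as a fixed effect would not help: ward is nested in study group, so the ward terms absorb the group contrast.
- **Not all of the power loss comes from correlation.** This is right. At ICC 0 the 8-df test already has 0.69 power, so at ICC 0.02 about half of the fall from 0.80 to 0.60 is due to degrees of freedom. That loss is still part of valid inference from five wards per group.
- **The ICC range is assumed, and pairing or baseline adjustment might recover precision.** Both are fair. Neither pairing nor baseline PES-NWI enters the calculation or the named tests. A paired ward-level test has only 4 df, and at ICC 0.05 its power is 0.40 if pairing removes no variance.
- **HS-EBP measures individuals.** The agreement argument is weaker there and no size was computed. The intervention is still given by ward, so the ward term is needed.
- **The study is described as exploratory, and the wards are fixed.** It nonetheless states an alpha, a power and a target difference, and its main objective is to evaluate impact. Fixed wards are why the remedy lies in the analysis and the stated power.

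**Conclusion.** The concern holds. The arithmetic behind 70 per group is correct for the model used, but the model is wrong for a comparison of five wards with five wards. The stated 5% error of a nurse-level test holds only if the within-ward correlation is zero, which is implausible for an organisational scale that was also used to select the wards. With a ward-level test, 80% power is not reached even at zero correlation.

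For ICCs of 0.02 to 0.20, the error of the nurse-level test is about 8% to 28% and valid power for 4 points is 60% down to 27%. These figures rest on the assumed ICC, equal ward sizes of 12.6 analysed nurses, the stated SD of 8, and no gain from pairing or baseline adjustment. The direction of the error does not depend on where in that range the ICC lies. This should be corrected before the PES-NWI comparison is reported.

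**What to change.** **Section 2.8.** For PES-NWI and HS-EBP, replace ANOVA or Kruskal-Wallis on nurses with a linear mixed model that has study group as a fixed effect, a random intercept for ward and Satterthwaite degrees of freedom. A comparison of the ten ward means is an acceptable alternative.

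**Section 2.5.** State that the ward is the unit of intervention. Restate the power for 4 points, and the difference detectable with 80% power, using a design effect over a declared ICC range and ward-level degrees of freedom. The January 2018 PES-NWI data can supply an ICC estimate. That estimate will be imprecise if it rests on ten wards and may be distorted because wards were selected on the score, so keep a range around it.

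**Cost.** New analysis wording and a restated power. No further wards or data are needed, and the MIXED procedure in the planned SPSS v.22 can fit the model. Intervals will widen and the stated power will be less favourable.

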### 2.6. Inclusion and Exclusion Criteria

Quantitative phase: the intervention wards were selected according to the baseline score obtained in the PES-NWI questionnaire, although no cut off points were established. Medical and surgical wards with a well-established leadership structure were included with the participation of each hospital’s nursing managers. Each intervention unit was paired with a control unit in the same hospital with similar characteristics and health indicators.

After the selection of hospital wards, project information meetings were held for the nursing teams, who were invited to participate. The nurses in each unit nominated one of their number, presenting the competencies needed to perform the role of the APHN, and another who provided support. Both participants had to be in a stable employment relationship in the unit. This selection was made from the nurses who applied to take part, according to their leadership qualities and APNCAI scores obtained (Supplementary Appendix 1). The supervisors of the wards were also part of the study subjects.

Qualitative phase: for the focus groups in the intervention groups, we select registered nurses who have worked throughout the entire intervention period. For the APHN focus group, the inclusion criteria is having been the APHN of the unit from the beginning of the project.

### 2.8. Data Analysis

Descriptive and exploratory analyses of the quantitative data will be performed, determining, among other parameters, the main indices of central tendency, dispersion, and shape. In addition, an analysis of missing values will be conducted. The association between variables will be determined according to the scale of their mean values. A stratified analysis will be carried out using the Mantel and Haenszel test, among others (stratifying according to the possible confounding variables). Bivariate analysis will be performed to detect significant associations between the main variables and sociodemographic, occupational, and complementary variables. Multivariate analysis will also be carried out using regression models. The mean values obtained will be compared by ANOVA or the nonparametric equivalent (Kruskal–Wallis test). The main variables will be crossed with the sociodemographic variables (age, gender), the occupational variables (hospital, unit, years of experience as a registered nurse), and the complementary variables (academic qualifications). These will be analysed as possible confounders and/or modifiers of the effects produced on the study variables. Finally, an exploratory analysis of lost data will be performed. The SPSS v.22 statistical software package ( SPSS Inc., Chicago, IL, USA) will be used for all these analyses.

For the qualitative phase, a realistic thematic analysis [40] of the focus groups transcriptions will be carried out. It will be used to generate a rich description of registered nurse and APHN views on how the change process evolved and impacted the unit and patients’ outcomes and how context jeopardized and/or facilitated the process. Two researchers will analyze the data across five phases: (1) through a first process if reading, initial themes and codes will be identified and grouped and emerging patters will be checked; (2) a second process of reading and re-reading, aimed at interpreting the themes, will be conducted; (3) at this point, the two researchers will share their interpretation and will reach consensus on the list of codes and sub-codes; (4) these codes will be rechecked through a third process of reading then pieces of text that exemplify the themes will be categorized under each code. Attention will be paid to new codes that may not have been identified earlier; (5) final patterns and links will be identified among themes and codes.

The “Atlas-Ti” tool will be used for the trees’ codification, and the results will be triangulated among other members of the research team. A review by the participants will also be requested (member checking).

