### 2.4. Variables

In the quantitative phase, four main study variables are addressed via Spanish validated instruments (Supplementary Appendix 1):-Organisational traits, measured by the Practice Environment Scale Nursing Work Index (PES-NWI) [37].-The nurses’ individual level of EBCP, measured by the Health Science Evidence-Based Practice Questionnaire (HS-EBP) [38].-Health indicators of the patients admitted to the study wards, derived from the clinical practice guidelines implemented by the APHNs in their wards and obtained by monthly clinical audits (Table 2).-The APHNs’ competence, as measured by the Advanced Practice Nursing Competency Assessment Instrument (APNCAI) [39].

In the qualitative phase, after 1 year of the APHN’s implantation, the nurses’ perceptions are explored regarding the evidence-based clinical practice and the impact on the health results of the patients (Table 2).

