### 2.9. Rigour and Validity

The randomization was not possible in this quasi-experimental study. Its strength lies in the controlled nature of the APN interventions and the continuous support offered in the form of permanent communication, training, and mentoring. The fact that the study is multicentre and was performed in very diverse contexts and at different levels from the type of patient to the type of organisation increases its external validity and means that a rich database of both quantitative and qualitative data will be obtained for analysis.

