	Nursing as the basis of the care process and the requirement for its continuity.	
	Patient scheduling and case management.	
	Supervising the results of health care and its impact on clinical management and interventions.	
	Training as the basis for clinical care for patients and their families.	
Promoting health care	Health policies, locally and internationally.	Attitude, Perceived control
	Techniques and strategies for promoting health.	
	Development and implementation of health promotion programmes for adolescents and adults.	
	Secondary and tertiary prevention for people with multiple or chronic health problems.	
	Promoting self-care within the family and/or providing support systems to facilitate their participation in health care.	
	Empowering the individual, groups and communities to adopt healthy lifestyles and self-care.	

**Table 2 ijerph-17-03473-t002:** Clinical indicators.

Indicators Derived from Clinical Practice Guidelines (CPG) for Pressure Ulcers (PU)				
	Indicator	Description	Definition	Data Collection Method
Structure indicators	Knowledge of the CPG	Awareness of the CPG within the unit	Number of nurses in the unit familiarised with the CPG × 100/number of nurses in the unit	By direct interview, performed annually.
	Material resource requirements	Wards presenting a material resource needs report	Dichotomous value. Does the unit present a needs report?	Audited by APNs, annually
Process indicators	Risk of PU	Assessment of PU risk in the target population, according to the Braden Scale	Number of patients at risk of PU according to the Braden scale × 100/number of hospitalised patients	By computer system and monthly APN audit
	Postural changes	Percentage of patients at risk of PU with an appropriate schedule of postural changes	Number of patients with scheduled postural changes × 100/number of patients at risk of PU	Monthly APN audit
	Pressure modification/Pressure relief support (PMS/PRS)	Percentage of patients at risk of PU and provided with PMS or PRS	Number of patients provided with a viscoelastic mattress × 100/number of patients at low, moderate and high risk of PU, according to the Braden scale	Monthly APN audit
Outcome indicators	Prevalence of PU	Percentage of patients with PU when the study was performed (or obtained monthly)	Number of patients with PU × 100/number of patients who met the criteria for inclusion in the study (hospitalised patients)	By computer system and monthly APN audit

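### Section 2.8 names no patient-level risk variable for the patient health indicators, so crude pressure ulcer rates stay open to case-mix bias between non-randomised wards

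*Protocol article*

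**What the plan says.** Section 2.4 lists four main study variables. Three are questionnaire scores from nurses. The fourth is "Health indicators of the patients admitted to the study wards, derived from the clinical practice guidelines implemented by the APHNs in their wards", which serves specific objective 3 in the Introduction.

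Section 2.8 does not separate them. It states that "The main variables will be crossed with the sociodemographic variables (age, gender), the occupational variables (hospital, unit, years of experience as a registered nurse" are to be examined against the main variables, "and the complementary variables (academic qualifications" completing the list. It adds: "These will be analysed as possible confounders and/or modifiers of the effects produced on the study variables". The Mantel-Haenszel analysis is stratified by possible confounders, and no others are named.

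On comparability, section 2.9 says "The randomization was not possible in this quasi-experimental study". Section 2.6 says "Each intervention unit was paired with a control unit in the same hospital with similar characteristics and health indicators". Section 2.2 gives each arm three medical and two surgical wards.

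Table 2 uses Braden risk in several places. As a process indicator it is "Number of patients at risk of PU according to the Braden scale × 100/number of hospitalised patients", taken from the computer system and the monthly audit. The pressure-relief indicator has as its denominator the "number of patients at low, moderate and high risk of PU, according to the Braden scale". Two of the four PU outcome indicators, prevalence and incidence according to risk, divide by patients at risk. Their descriptions speak of at-risk patients who have or develop an ulcer, but the formulas place no such limit on the numerator.

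**The concern.** Years as a registered nurse and academic qualifications can only describe nurses. Age and gender stand in the same list, and the text does not say whose they are. Hospital and unit are setting variables, but they do little for the comparison of arms: hospital is already matched by the pairing, and each unit lies wholly in one arm, so adjusting for unit cannot separate the arm effect from ward differences. If the list is followed as written, nothing in it represents how prone the admitted patients were to pressure ulcers.

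This matters because the Discussion expects lower complication incidence in intervention wards as the result of the advanced practice hospitalization nurse (APHN) role. A difference in admission mix could produce that pattern or hide it. The pairing was done when wards were selected and cannot hold the mix equal over the months of audits that followed. The limitations in the Discussion cover informal leadership and contagion, not case mix.

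**Working it through.** **The plan's own figure.** The only sample size stated is 70 nurses per group, for the PES-NWI (section 2.5: difference 4, SD 8, two-sided alpha 0.05, power 80%, 10% loss). n = 2 × (1.96 + 0.84)² × 8² / 4² ≈ 62.7, so 63; 63 / 0.90 = 70. It reproduces. It does not concern the patient indicators and is unaffected by this point.

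**Inputs for the bias.** The documents give no PU rates and no Braden distribution, so all inputs below are assumptions. Incidence is the same in both arms within each risk group, so the true ratio is 1.00.

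**Illustration 1.** Assumed incidence is 1% (no or low risk), 4% (moderate) and 10% (high). Crude incidence = sum of share × incidence:

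- 60/25/15 mix: 0.60×1 + 0.25×4 + 0.15×10 = 3.1%
- 50/30/20 mix: 0.50×1 + 0.30×4 + 0.20×10 = 3.7%
- 40/35/25 mix: 0.40×1 + 0.35×4 + 0.25×10 = 4.3%

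The at-risk rates below count moderate and high risk as at risk. The limited version uses ulcers in those patients only (2.5/40, 3.2/50, 3.9/60). The printed version uses all new ulcers (3.1/40, 3.7/50, 4.3/60).

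| Mix | Crude (ratio) | At-risk rate, numerator limited (ratio) | At-risk rate, formula as printed (ratio) |
|---|---|---|---|
| 60/25/15 | 3.1% (1.00) | 6.25% (1.00) | 7.75% (1.00) |
| 50/30/20 | 3.7% (1.19) | 6.40% (1.02) | 7.40% (0.95) |
| 40/35/25 | 4.3% (1.39) | 6.50% (1.04) | 7.17% (0.92) |

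If the lower-risk mix is in the intervention wards, the crude ratios invert to 0.84 and 0.72.

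**Illustration 2.** Two groups only, with assumed incidence at risk / not at risk of 8/1%, 10/1% or 15/2%, and 30% at risk in intervention wards. With 35%, 40% or 50% at risk in control wards, the crude ratio is 0.89–0.90, 0.80–0.82 or 0.67–0.69. For example, at 10/1% and 40%: (0.30×10 + 0.70×1) / (0.40×10 + 0.60×1) = 3.7/4.6 = 0.80. The printed at-risk formula gives (3.7/0.30) / (4.6/0.40) = 12.33/11.50 = 1.07 in that case and 1.04 to 1.16 over the whole range. Mix alone can therefore make the two indicators point in opposite directions. Stratifying by at risk or not returns 1.00 throughout.

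**Illustration 3.** Severity within the at-risk group, with the numerator limited and assumed incidence 3/8/20% at low/moderate/high risk. Mixes 60/30/10, 50/30/20 and 40/30/30 give 6.2%, 7.9% and 9.6%. The ratios are 6.2/7.9 = 0.78 and 6.2/9.6 = 0.65. A single at-risk group may therefore leave bias, which is why grade is worth using where it was recorded.

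**The case against.** A reader might infer that the plan uses no patient-risk variable at all. It does: two of the four PU outcome indicators have Braden at-risk denominators. What holds is narrower: section 2.8 names none for adjustment or stratification. A reader might also infer that every listed variable is a nurse trait. Hospital and unit are not, and the owner of age and gender is unstated.

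The design offers real control. Pairing was within hospital and on health indicators as well as characteristics, and ward type is balanced between arms. The larger ratio of 1.39 needs a 20-point shift out of the lowest risk group between wards chosen to be alike. This reduces the likely bias but does not address admissions after selection.

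It would also be wrong to carry 1.19 to 1.39 over to the risk-specific indicators. On the same inputs these give 1.02 to 1.04 with the numerator limited, and 0.95 to 0.92 as printed. Other within-group mixes can do worse, as Illustration 3 shows.

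Braden is not a clean adjuster either. Its assessment is a process indicator of the guideline being implemented, so scoring may shift in intervention wards.

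Finally, this is a condensed article, its analysis is called descriptive and exploratory, and nothing in it forbids using Braden. A full model specification is indeed not to be expected here. The article does, however, state a list and apply it to outcomes it does not fit, which is more than an omitted detail.

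**Conclusion.** The point stands in limited form. Section 2.8 gives the patient health indicators a confounder list designed for nurse questionnaires, plus hospital and unit, with no patient-level risk variable. Crude PU prevalence and incidence therefore remain open to case-mix bias despite the pairing and the ward-type balance. The two risk-based indicators do not close the gap, because their printed numerators are not limited to at-risk patients.

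Under Illustration 1 the crude incidence ratio is 1.19 to 1.39, or 0.84 to 0.72, with no true effect. These figures rest wholly on assumed rates and mixes, concern the crude rate only, and do not predict the bias in this study or its direction. The documents do not show that the wards actually differed in patient risk. The change should be made, but the point does not undermine the questionnaire comparisons.

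**What to change.** In section 2.8, give the PU outcomes their own adjustment set:

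- Use the planned Mantel-Haenszel or regression analysis, stratified by or adjusted for Braden risk: at risk or not as a minimum, by grade where recorded. Take the admission or first recorded score where available. Keep hospital or ward pair in the set.
- In Table 2, limit the numerators of both risk-specific PU indicators to at-risk patients, in line with their descriptions.
- Report the Braden mix per ward and month beside the rates.
- Use nurse experience and qualifications only for the nurse questionnaires.
- Report unadjusted rates alongside, and state that Braden scoring may itself respond to the intervention.

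The cost is mainly wording, since Braden risk already comes from the computer system and the monthly audit. The article does not say whether grade or a first score is kept per patient, so the finer stratification depends on what was stored. The Braden adjustment does not cover the catheter outcomes. The article should say that these remain without patient-risk adjustment unless a suitable variable was recorded.
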